**Newsletters**			

- 4 Newsletter	4 newsletters are sent by mail with information about health behaviour change following HAPA framework and tips for healthy eating and increasing physical activity.		Focus of the 4 newsletters: 1. outcome expectancies and self efficacy 2. Self efficacy, coping with barriers. 3. Intentions and maintenance 4. Maintenance

Like PRISMA, DiAlert encourages participants to consider their personal risk factors and choose specific goals of behaviour changes by using a non-didactic learning approach. Through eliciting personal stories and respectfully exploring and discussing participants 'personal models' [26] and barriers, the stage is set for reviewing the need for and benefits of behaviour changes, with a focus on healthy food choices and increasing leisure physical activities resulting in a personal action plan to change health behaviour.

A participant manual was developed after investigation of printed education materials of other lifestyle interventions and health promotion leaflets. The manual provides background to sessions and contains information about diabetes prevention, including risk information, tips and tricks to enhance self-efficacy and outcome expectancies for diet and physical activity, resources for the participants such as a table of caloric values and worksheets for the homework assignment and the participants' action plan. In addition, four newsletters will be sent by mail during the follow-up (see Figure 1) providing information on health behaviour change, links to relevant websites, and 'tips and tricks' to stay on track with behavioural changes, physical activity resources in the neighbourhood and recipes for healthy cooking.

To enhance effectiveness and sustainability, participants will be informed about and encouraged to use existing local facilities for healthy lifestyle programs. Participants will be stimulated to seek support after DiAlert from their GP, a dietician or physiotherapist to assist them with their goals to lose weight.

### Pre-testing the intervention

Once the initial draft of the DiAlert intervention was completed, the intervention was pre-tested by a multidisciplinary panel of diabetes professionals, consisting of a registered dietician, a diabetes nurse specialist, two specialist diabetes psychologists, a research assistant, and an expert in the field of diabetes risk communication. The intervention was delivered by a trained psychologist and a health scientist (WH), both certified PRISMA trainers. The feedback from the professionals' panel was overall positive with minor suggestions for further improvement.

Following a framework for development and evaluation of RCTs for complex interventions to improve health (MRC framework) [27] a feasibility and piloting stage was be performed before embarking on a randomised controlled trial. Twenty first degree relatives of T2DM patients were invited to participate in a pilot study to evaluate feasibility, acceptability, participant appreciation, and questionnaire assessments. Based on the evaluation of the pilot the intervention modules were adapted before we set off the RCT.

### Cultural adaptation

After implementation of DiAlert in the ethnic Dutch population, we will assess effectiveness and feasibility of DiAlert in a population of Turkish people who live in the region of Amsterdam in the Netherlands. Cultural adaptation and translations will be performed in order to target DiAlert for this group. By means of a needs assessment general information about the community, demographic data, health status, knowledge of health and cultural related information will be obtained [28]. Possible 'mismatches' in the ethnic Dutch intervention will be identified through literature review, interviews and focus group discussions with lay people from Turkish descent.

Study materials including participant information, newsletters and leaflets will be translated into Turkish with regard to core values, beliefs, norms and other significant aspects of the groups and lifestyles [29].

Questionnaires will be forward-translated by a bilingual health professional with knowledge of both the Dutch and Turkish culture, following guidelines of the WHO for translating instruments [30]. Conceptual rather than literal translations will be taken into account by natural and acceptable language. Backward-translations will be performed by an independent translator whose mother tongue is Turkish. Comparisons between the two translations will be performed and discrepancies will be discussed with both translators.

A pilot test of the culturally targeted intervention will be carried out in a sample of the target population to pre-test study materials and modules of DiAlert. Fidelity and appreciation will be evaluated with questionnaires and interviews.

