**Methods/design:**

In this RCT, 268 (134 Dutch and 134 Turkish) overweight 1st degree relatives of patients with T2DM will be allocated to either the intervention or control group (leaflet). The intervention DiAlert aims to promote intrinsic motivation to change lifestyle, and sustain achieved behaviour changes during follow-up. Primary outcome is weight loss. Secondary outcomes include biological, behavioural and psychological indices, along with process indicators. Measurements will take place at baseline and after 3 and 9 months. Changes in outcomes are tested between intervention and control group at 3 months; effects over time are tested within and between both ethnic groups at 3 and 9 months.

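### The mother-tongue rule for translating the questionnaires is placed on the back-translator, who reads Turkish, and not on the forward translator, who writes it; this may weaken a quality check on some secondary outcomes (minor)

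*Protocol article*

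**What the plan says.** The translation procedure is in the Protocol article under Cultural adaptation.

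- **Direction.** For the study materials: "Study materials including participant information, newsletters and leaflets will be translated into Turkish". The questionnaires are adapted for the same group, so their forward step also ends in Turkish.
- **Forward step.** "Questionnaires will be forward-translated by a bilingual health professional with knowledge of both the Dutch and Turkish culture, following guidelines of the WHO". No mother tongue is named.
- **Backward step.** "Backward-translations will be performed by an independent translator whose mother tongue is Turkish". This translator's command of Dutch is not described.
- **Comparison.** "Comparisons between the two translations will be performed and discrepancies will be discussed with both translators".
- **Pilot.** "A pilot test of the culturally targeted intervention will be carried out in a sample of the target population to pre-test study materials". The programme modules are pre-tested too. The questionnaires are not named among the things tested.

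Other sections set the scope. The Abstract gives the sample ("In this RCT, 268 (134 Dutch and 134 Turkish) overweight 1st degree relatives") and the planned tests ("effects over time are tested within and between both ethnic groups at 3 and 9 months"). Outcome measures makes change in body weight the main outcome. Questionnaires says that cross-culturally validated instruments are used where possible. Study population accepts literacy in either Dutch or Turkish.

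**The concern.** A back-translation is meant to show whether the translated items carry the meaning of the source. It can do so only if a fault in the Turkish wording comes through into the Dutch text, where it can be seen against the source.

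The plan places native competence on the reading side of this check. A native Turkish reader may recognise what an awkward or slightly wrong item was meant to say and write that intended meaning in Dutch. The back-translation then agrees with the source although the item is faulty. The step where native Turkish would help most directly, the writing of the items, carries no such requirement.

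At stake are the behavioural, psychological and health-status outcomes collected by questionnaire, and predictors such as perceived risk. A faulty Turkish item cannot be repaired once the data are in.

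**Working it through.** The plan states no figure for this point, so the check is mainly one of reasoning. The only arithmetic is the share of participants affected.

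**1. Which language each translator reads and writes**

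| Step | Reads | Writes | Stated language requirement |
|---|---|---|---|
| Forward | Dutch (inferred) | Turkish | Bilingual; knows both cultures |
| Backward | Turkish | Dutch (inferred) | Mother tongue Turkish; independent |

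The source language is not named. Dutch is inferred because the trial runs first in the Dutch group and the forward translator must know both cultures. On that reading the mother-tongue rule sits on the language being checked and not on the language being written.

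**2. Whether a later check would catch a silently repaired item**

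- The discussion with both translators starts from discrepancies. A repaired item produces none.
- The Turkish pilot covers materials and modules. Questionnaires appear there as tools for judging fidelity and appreciation, not as objects of the test. By contrast, the pilot described under Pre-testing the intervention lists questionnaire assessments among the things evaluated.
- Existing cross-cultural validation helps where it exists, but it is promised only where possible. The food frequency instrument is a modified version (Lifestyle behaviours), and risk-perception questions are derived from other instruments (Determinants of health behaviour change). For such items an earlier validation may not carry over.

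So the later checks reduce the risk but do not clearly remove it.

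**3. How many participants could be affected**

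Inputs: 134 Turkish-origin participants of 268 in total (Abstract). Upper bound: 134/268 = 50%. The share *u* of the Turkish group who would answer in Turkish is not given. With *u* as an assumption, the share of the whole trial is *u* × 134/268:

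| *u* (assumed) | Share of all participants |
|---|---|
| 25% | 12.5% |
| 50% | 25% |
| 75% | 37.5% |
| 100% | 50% |

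These are shares of participants, not of outcomes. Among outcomes, only newly translated or modified instruments count.

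**4. What a faulty item would do to the analyses**

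Write the observed Turkish score as *a* + *b* × (true score) + error.

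- *Arms within the Turkish group.* Both arms answer the same items, so *a* cancels in the contrast between arms. What remains is extra error and, if *b* is below 1, a diluted effect.
- *Change over time, Dutch against Turkish.* Change = (*a* + *b*·T₂) − (*a* + *b*·T₁) = *b*·(T₂ − T₁), apart from error. A constant shift *a* cancels. Only altered responsiveness (*b* different from 1) or added error affects this comparison.
- *Score levels, Dutch against Turkish.* Here *a* does not cancel, so levels at one time point are less comparable.
- *Body weight.* It is measured on scales, so nothing changes.

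**The case against.** The strongest reply is that nothing in the article contradicts itself, and that the harm is a hypothesis about how translators behave. A native Turkish reader may equally well notice unnatural Turkish and raise it, and the article's aim of natural, acceptable language suits such a reader. The translator may also be fully bilingual, since the article is silent on command of Dutch and does not say it is weak. The safeguards are more than token: the forward translator is a bilingual health professional who knows both cultures and follows guidelines, the back-translator is independent, and a pilot in the target group is planned.

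Most of this stands as a limit on size. It shows that the harm is uncertain. It does not show that the check is well placed, because flagging bad Turkish is not the back-translator's stated task, whereas rendering its meaning is. Nor is this a complaint about omitted detail: the article positively states the mother tongue.

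Three stronger readings are tempting, and the documents support none of them.

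- *Half of the trial's questionnaire outcomes rest on these translations.* Half is the Turkish share of participants and an upper bound. Participants literate in Dutch could answer in Dutch, and validated instruments may cover part of the questionnaire.
- *The trial loses power.* The article gives no reliability for any scale and makes no power claim for questionnaires. Its effect and SD, 3.5% and 6%, belong to body weight. Any figure would combine assumed reliabilities with an effect size borrowed from another outcome.
- *The comparison of effects between ethnic groups is biased by a shifted scale.* A constant shift cancels in change scores and in contrasts between arms.

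A reader might also infer that only the two translators may resolve discrepancies. The text says they take part and excludes nobody. Whether the choice departs from the cited guideline cannot be judged from the article, and the point does not rest on it.

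**Conclusion.** The point holds as a minor weakness in a stated procedure. The mother-tongue requirement is on the step that reads Turkish, none is set for the step that writes it, and a fault repaired in reading would leave no trace for the later comparison.

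Its reach is limited to secondary questionnaire outcomes and predictors that are newly translated or modified, among Turkish-origin participants who use the Turkish version: at most 134 of 268, and fewer if some answer in Dutch. The likely consequence is added measurement error within the Turkish group and weaker comparability of questionnaire scores between the ethnic groups. The primary outcome and the sample size are untouched.

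The conclusion assumes that the questionnaires, like the other materials, go from Dutch into Turkish, and that a native reader may sometimes repair wording without flagging it. How often that would happen is unknown.

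**What to change.** Amend the translation paragraph under Cultural adaptation in three places.

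1. Have the backward translation into Dutch done by an independent translator who is a native Dutch speaker, is fluent in Turkish and has not seen the source questionnaire.
2. Require Turkish as mother tongue for the forward translator, in addition to the qualifications already listed.
3. Name the translated questionnaire items among the materials tested in the Turkish pilot, so that members of the target group read them before use.

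It would also help to list which instruments rest on this translation and which come in an existing validated Turkish version.

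The cost is close to nil. There are still two translators and one comparison, the pilot is already planned, and the article describes this work as still to come. Sample size, error rate and analysis model stay as they are.

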### Outcome measures

The main outcome measure is change in body weight. Secondary outcome measures include biological, behavioural and psychological outcomes and perceived health status. Predictors for weight loss and health behaviour change (e.g. participant characteristics: gender, initial BMI, SES, number of family members with diabetes, perceived risk and perceived seriousness of diabetes) will be assessed.

### Measurements

Baseline measurements are planned after randomisation and follow-up measurements are planned at 3 and 9 months (see Figure 1 for a detailed flowchart). Baseline and follow-up measurements include physical measures, laboratory tests and questionnaires.

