**Figure 1 F1:**
[figure not shown]
**Participant flow**. A detailed participant flowchart of the DiAlert study

Information is lacking on the standard deviation of the percentage of weight change over 3 and 9 months of follow-up in a population at risk for T2DM due to family history and overweight. This study is powered to detect a difference of at least 3.5% body weight at 3 months after randomisation (derived from DPP [8]). Assuming a conservative standard deviation of 6%, a power of 80%, and a significance of 0.05 we require a sample size of 50 participants per group at that time point. If during initial screening T2DM is assessed participants will be excluded from the study (10%). Furthermore, we assume an attrition rate of approximately 15%. Therefore we aim to over sample (25%), and include 67 persons in each group (Dutch group: 67/67 Turkish group: 67/67)

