### Treatment allocation

After receiving a signed informed consent form from the participants, randomisation will be performed with sealed envelopes. Members of the same family or household participating in the study will be clustered. This will be done to stimulate cohesion in the intervention groups, and to prevent contamination of the intervention effect due to reciprocal communication about the intervention or control condition among family members.

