#### Laboratory tests

Fasting blood samples will be drawn at the laboratory to determine HbA1c, total cholesterol, LDL and HDL-cholesterol, triglycerides, glucose and insulin, to calculate HOMA [31].

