## Discussion

This randomised controlled trial is designed to evaluate the effectiveness of DiAlert in assisting overweight individuals with a family history of T2DM to lose weight in order to reduce their risk of developing T2DM. There is growing evidence for prevention of T2DM by lifestyle. However, an approach with a focus on family history combined with structured lifestyle education has not been utilized before. We assume that the DiAlert intervention will prove to be more effective than the control condition in achieving significant body weight loss at 3 months and 9 months. In addition, we expect to observe significant changes in metabolic, psychological and behavioural parameters following the intervention in both ethnic groups, resulting in reduced risk of developing T2DM.

The study has some limitations that should be mentioned. First, blinding of the participants will be impossible because they receive the intervention. To limit this bias, participants will not be informed about the outcomes of measurements, except when outcomes suggest diagnosis of diabetes based on guidelines. Furthermore, family history and overweight is not consistently recorded in patient registers of the GP in the Netherlands [42], which might hinder recruitment of participants. Therefore we will utilise different recruitment strategies. By recording the recruitment path of each participant, we will be able to take into account bias due to different motivations of participation in the study.

Despite the growing knowledge in the field of primary prevention, there is an urgent need for well-designed translational studies in populations at high-risk for diabetes. The challenge in offering an intervention in a primary care setting is to find the right balance between efficacy (intensity, follow-ups) and feasibility. Particularly, in the case of people who are just at risk for T2DM and not yet medically ill and not meeting with disadvantages and complications of the disease. To increase feasibility, the intervention will be delivered in close proximity to participants' homes, which could reduce barriers for participation. In addition, because DiAlert consists only of two interactive group sessions, we assume low drop-out rates. At last, delivery in GP practices or in the outpatient clinic could contribute to the perception of the reliability of the given information.

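### Baseline weight and baseline questionnaires are taken after randomisation in an unblinded trial, with no stated concealment of allocation until they are done

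*Protocol article*

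**What the plan says.** Treatment allocation gives the first step: "After receiving a signed informed consent form from the participants, randomisation will be performed with sealed envelopes". No measurement is placed between consent and randomisation. Measurements gives the next: "Baseline measurements are planned after randomisation and follow-up measurements are planned at 3 and 9 months". It also says what baseline contains: "Baseline and follow-up measurements include physical measures, laboratory tests and questionnaires". Outcome measures makes change in body weight the main outcome, so the reference value for the primary analysis is one of these post-randomisation measurements.

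On blinding, the Discussion says "First, blinding of the participants will be impossible because they receive the intervention". The remedy it offers is to withhold measurement results from participants unless they point to diabetes. Physical measures has a trained research assistant do the weighing and does not mention blinding of that person.

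On eligibility, the sample-size text under Study design says "If during initial screening T2DM is assessed participants will be excluded from the study (10"%), adds "we assume an attrition rate of approximately 15"%, and concludes "Therefore we aim to over sample (25%), and include 67 persons in each group". The only glycaemic tests described are under Laboratory tests: "Fasting blood samples will be drawn at the laboratory to determine HbA1c, total cholesterol, LDL and HDL-cholesterol, triglycerides, glucose and insulin".

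**The concern.** A baseline value is safe from the effects of allocation only if it is recorded before the arm is known. Here the order is consent, randomisation, baseline. Three things could go wrong.

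- **Attendance.** Setting lets people enrol by e-mail or a mailed form, whereas baseline requires a visit to a practice, clinic or laboratory. One arm is offered a group course and the other written information. If people know their arm, turning up for the first visit may depend on it. Anyone who never attends has no observations at all.
- **Behaviour.** A participant who starts to change diet on learning the arm alters the baseline weight itself.
- **Self-report.** Intention, self-efficacy and risk perception are rated at the same baseline, and such ratings are more open to knowledge of allocation than a weight is. Outcome measures also names perceived risk as a predictor of weight loss.

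Withholding measurement results addresses none of these. No later analysis can recreate a weight that was not taken before allocation.

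**Working it through.** **1. Order of events.** Treatment allocation and Measurements, read together, give consent, then randomisation, then baseline. This is stated outright and needs no inference.

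**2. When participants learn their arm.** The text says that sealed envelopes are used. It does not say when the result is disclosed, and Figure 1 is not available. Disclosure before weighing is therefore possible but not stated, and no safeguard against it is described.

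**3. When diabetes is tested for.** The phrase about initial screening carries no date. Three facts point to testing after randomisation:
- randomisation follows consent directly;
- HbA1c and fasting glucose appear only among laboratory tests that belong to the baseline and follow-up measurements;
- the 10% exclusion is part of the number per arm, and the Abstract describes all 268 as allocated.

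**4. The plan's sample size.** Inputs from Study design: difference 3.5% of body weight, SD 6%, power 80%, significance 0.05 (two-sided assumed, as the text does not say).
- Normal approximation: n = 2 × (1.96 + 0.84)² × 6² / 3.5² = 46.1, rounded up to 47 per arm.
- t-test solution: 47.1, rounded up to 48 per arm.
- The stated 50 is slightly above both and gives about 83% power.
- Inflation: 50 / (1 − 0.25) = 66.7, rounded up to 67. This matches the plan and shows that the 25% is the 10% exclusion plus the 15% attrition.

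The calculation is sound. The problem is the order of events and not the number of participants.

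**5. Planned exclusions, if testing follows randomisation.**
- Per arm: 0.10 × 67 = 6.7, about 7.
- Whole trial: 0.10 × 268 = 26.8, about 27.

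**6. Numbers if exclusion comes before randomisation.** Only the 15% attrition then applies to randomised people.
- Randomised per arm: 50 / 0.85 = 58.8, rounded up to 59.
- Randomised per ethnic group: 2 × 59 = 118, or 236 in total.
- Screened per ethnic group: 118 / 0.90 = 131.1, rounded up to 132, or 264 in total.

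These fit within the planned 134 and 268.

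**7. Size of the bias.** The document gives neither the interval between allocation and baseline, nor any pre-baseline weight change, nor attendance by arm. No figure can be derived. The direction is open too. Early dieting in the intervention arm would lower its baseline and shrink the measured effect, while selective non-attendance could move the estimate either way.

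**The case against.** The strongest case on the other side has four parts.

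- **Disclosure is not stated.** The bias needs someone to know the arm before weighing. The article is condensed and its flowchart is not available, so silence does not prove disclosure. This stands: a reader might infer that the envelope is opened in front of the participant before baseline, but the text does not say so. The order itself, however, is a stated rule, and no safeguard accompanies it.
- **Screening may come first.** Folding 10% into a recruitment target is also how articles loosely present screening loss. This stands in part. The inference is strong, but it remains an inference.
- **The exclusions need not bias anything.** Undiagnosed diabetes precedes allocation and is found by a laboratory test, so exclusions should balance if both arms attend and are tested alike. This stands. A reader might infer that about 27 exclusions destroy the protection of randomisation; the documents do not support that.
- **The analysis can keep incomplete cases.** Statistical analysis plans mixed models over time, which could retain people who have follow-up weights but no baseline. This stands, so it is too strong to say that nobody without a baseline can be analysed as randomised. People who are never measured are still lost.

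A reader might also suppose, from the clustering of family members, that relatives who join later enter an arm already known to the household. Treatment allocation says only that members of a family or household are clustered. It mentions no later enrolment.

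**Conclusion.** The point holds in limited form. It is certain from the text that the baseline weight behind the primary outcome, and the self-reported baseline scores, are taken after randomisation in a trial with unblinded participants. It is also certain that no concealment until baseline is described. The threat is arm-dependent attendance or behaviour before weighing. It depends on allocation becoming known in that interval, and neither its size nor its direction can be determined from the document.

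That eligibility testing also follows randomisation is a strong inference. If it is right, the plan expects about 7 exclusions per arm, or 27 of 268, after allocation. That count rests on the plan's assumed 10% and measures planned removals, not bias. The sample size is adequate either way. The order should still be corrected, because it bears on the primary endpoint and cannot be repaired once participants have been allocated.

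**What to change.** **Preferred.** Change the order to: consent; baseline weight, questionnaire and fasting bloods; exclusion of those found ineligible; then allocation of the participant, or of the household where members take part together. State that the 10% is screening loss and set the numbers at about 132 screened and 118 randomised (59 per arm) per ethnic group.

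**If the order cannot be changed.** Conceal allocation from participants and assessors until baseline is complete. Decide exclusions on a pre-specified laboratory criterion, blind to arm. Report exclusions and losses before baseline by arm.

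**Cost.** A protocol amendment, with no extra visits or participants. Allocation has to wait for baseline results, which means some scheduling effort where several household members take part. Some people will be measured and then not randomised. If the Dutch part has already started, a change made only for the Turkish part would give the two ethnic groups different procedures. This should be stated when they are compared, and concealment until baseline may then be the more practical option.
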